**Background and Justification:**

Snake bite is a common problem in the rural tropics and is responsible for approximately two million snake envenoming worldwide each year (1).This means that large amounts of antivenom are administered in the treatment of snake envenoming. Unfortunately snake antivenom is made from foreign protein

(most commonly equine sources) and are associated with allergic reactions in a proportion of cases. The frequency of allergic reactions depends on the purity and source of the antivenom. It has also been suggested that the rate of infusion effects the frequency or risk of antivenom reactions. . Unfortunately the manufacture of high quality antivenom with low reaction rates is cost prohibitive in many parts of the world, so many antivenoms have reaction rates of 30-80%. The severity and frequency of these reactions has lead to increasing use of premedications to attempt to prevent allergic reactions. There have been routine recommendations of antihistamines, hydrocortisone and adrenaline for premedication (2).

The efficacy of premedication for antivenom administration is controversial with three recent controlled studies having differing results (2-4).It has been suggested that the rate of antivenom infusion may effect the chance of allergic reactions and that rapid infusions may cause complement mediated reactions. There are no studies that have investigated the effect of the rate of antivenom infusion on reaction rates.

There are no published systematic reviews on antivenom infusion rate and the risk of antivenom reactions. It is generally agreed by experts that the rapid administration of antivenom (particularly undiluted) will lead to early complement –mediated reactions (5). One study reported the adverse effects following the administration of redback spider antivenom in over 2000 cases.(6) In this report there were 11 cases defined as ‘anaphylactic’ reactions (0.54%) and in five of theses antivenom was given undiluted and is the likely cause of the reactions.

There is therefore no good evidence as to whether the rate of infusion affects the risk of allergic reactions. It is important to know this because rapid administration of antivenom is often important in severe envenoming to prevent life threatening effects and complications of envenoming. If slower and diluted infusions of antivenom are proved to be safer then consideration of infusion rate will become an important factor in the treatment of snake envenoming, otherwise rapid infusion would be the more appropriate approach if it does not increase the reaction rate.

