**ii. Detailed description of the research method.**

All patients bitten by a snake will be eligible for the study and will be approached at the time of admission, however they will not formally enter the interventional trial until the decision is made to administer antivenom. All eligible patients will have baseline clinical data collected, including clinical symptoms, signs and a 20 minute whole blood clotting test (20 WBCT). Baseline blood will be collected (see below). When a decision to administer antivenom is made, the patient will be randomized to one of the two parallel treatment arms. Patients in the first treatment group will receive 10 vials of antivenom in 500 ml of normal saline over 20 minutes [alternatively 20 vials of antivenom in 500 ml of normal saline over 40 minutes] Patients in the second treatment group will receive 10 vials of antivenom in 500 ml of normal saline over 2 hrs [alternatively 20 ampoules of antivenom in 500 ml over 4 hours.]

Randomisation will be done by computer in blocks of four (eg. AABB, ABAB etc.) using Microsoft Excel. The computer generated list will be used to randomize pieces of papers to sequentially ordered envelopes with the wording “20 minute infusion” or “2 hour infusion”

Patients will be closely observed for the four hour period following the commencement of administration of antivenom. The patient will be put on a cardiac monitor for this period if possible. For the first hour, HR, BP, RR, oxygen saturation and temperature will be measured every 5 minutes and then every hour for the remainder of the four hours. Patients will be observed for evidence of an allergic reaction using the Brown grading system,(10) including auscultation of the chest. Allergic reactions will be treated as per the current protocol of antivenom reactions with intravenous fluids and 0.5 mg of intramuscular adrenaline into the lateral thigh (or upper arm if not possible).

A 15 mL sample of blood will be taken using a sterile technique (syringe and needle) from each patient.

- 1. The 15mL sample will be divided between one serum (red top tube), one EDTA tube (purple top) and one plasma citrate (blue top) tube.
  2. The serum tube will be spun and the serum aliquoted into 3 portions and frozen.
  3. The citrate plasma tube will be immediately double spun and then aliquoted into two separate tubes and immediately frozen.
  4. The EDTA tube will be spun and aliquoted into two separate containers.

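### Premedication is neither fixed nor recorded although the arm is known before antivenom starts, so use could differ by arm; the risk is real but its size and direction are unknown

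*Protocol*

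**What the plan says.** The Background and Justification section presents premedication as a live practice directed at the reactions this trial counts: "The severity and frequency of these reactions has lead to increasing use of premedications to attempt to prevent allergic reactions", and "There have been routine recommendations of antihistamines, hydrocortisone and adrenaline for premedication". It also doubts the benefit: "The efficacy of premedication for antivenom administration is controversial with three recent controlled studies having differing results".

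On allocation, the detailed description of the research method says "When a decision to administer antivenom is made, the patient will be randomized to one of the two parallel treatment arms". A computer-generated list is used to "randomize pieces of papers to sequentially ordered envelopes with the wording" of the infusion duration, 20 minutes or 2 hours. The Research Plan calls the trial both open label and double-blind, but no dummy infusion or other masking is described. The admitting consultant remains responsible for the patient throughout.

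The only rule on anti-allergy drugs concerns reactions that have already occurred: "Allergic reactions will be treated as per the current protocol of antivenom reactions with intravenous fluids and 0.5 mg of intramuscular adrenaline". The exclusion criteria do not mention premedication. The section on medical procedures and safety measures neither requires, forbids nor records it. The analysis section names initial antivenom dose and earlier antivenom as factors to be modelled, and does not name premedication.

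**The concern.** Premedication is meant to prevent the event that forms the primary outcome, a grade 3 reaction within 4 hours of starting antivenom. Whoever decides on it can already know which infusion the patient will receive. If the decision depends on the arm and the drugs work, the trial compares infusion rate plus a different amount of premedication. Intention-to-treat keeps patients in their allocated arm, but it does not remove the effect of a drug given unequally after allocation. A later analysis plan could not recover data that were never collected.

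The protocol's list of measures against bias claims to be complete. Its six items cover the sequence, unpredictability of allocation, objective outcomes, recording by the study team, follow-up and intention-to-treat. None covers drugs given after allocation.

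The direction matters for the decision. Heavier use in the 20-minute arm would shrink a true benefit of slow infusion towards no difference. The Background says how such a result would be read: "otherwise rapid infusion would be the more appropriate approach if it does not increase the reaction rate". Heavier use in the 2-hour arm would make slow infusion look better than it is.

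**Working it through.** **Inputs from the protocol.** The sample size section gives 50% vs 30%, alpha 5%, power 80%, a minimum of 103 per arm, and a recruitment aim of 240, which is 120 per arm. The true slow/fast risk ratio under the hypothesis is 0.30/0.50 = 0.60.

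**Inputs that are assumptions.** The protocol gives neither premedication uptake nor its effect. The main illustration takes uptake of 50% in one arm and 20% in the other, and a risk ratio r = 0.8 for a reaction with premedication. Sidedness is not stated, so a two-sided test is assumed.

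**Step 1: the protocol's own figure.** The two-proportion formula for 50% vs 30%, two-sided 5%, 80% power, gives 93 per arm without continuity correction and 103 with it. The stated 103 is therefore reproduced with the correction, and the power figures below use the same form: n' = n × (1 − 1/(n × d))², where d is the difference in proportions. At n = 103 and d = 0.20, n' = 93.2 and power is 80.1%.

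**Step 2: effect on the risk ratio.** If a share p of an arm is premedicated, that arm's risk is multiplied by 1 − (1 − r) × p. The observed slow/fast ratio is the true ratio multiplied by

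(1 − (1 − r) × p_slow) / (1 − (1 − r) × p_fast).

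This factor is 1 if r = 1 or if uptake is equal. With r = 0.8:

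- 50% fast, 20% slow: 0.96/0.90 = 1.067; 0.60 × 1.067 = 0.640.
- 20% fast, 50% slow: 0.90/0.96 = 0.938; 0.60 × 0.938 = 0.562.

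**Step 3: effect on power.** Rates are scaled so that equal uptake at the mean of 35% gives exactly 50% vs 30%. The scaling constant is k = 1 − 0.2 × 0.35 = 0.93.

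- Heavier use in the 20-minute arm: 0.50 × 0.90/0.93 = 48.4% and 0.30 × 0.96/0.93 = 31.0%. Power is 67.7% at 103 per arm and 75.1% at 120.
- Heavier use in the 2-hour arm: 0.50 × 0.96/0.93 = 51.6% and 0.30 × 0.90/0.93 = 29.0%. Power is 89.1% at 103 per arm and 93.5% at 120. The gain is not a benefit, because it comes from an exaggerated effect.

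**Step 4: sensitivity to the assumptions.** Continuity-corrected power at 103 per arm:

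| Uptake fast / slow | r | Observed ratio | Power |
| --- | --- | --- | --- |
| equal | any | 0.60 | 80% |
| 40% / 30% | 0.8 | 0.61 | 76% |
| 40% / 30% | 0.6 | 0.63 | 72% |
| 50% / 20% | 0.8 | 0.64 | 68% |
| 50% / 20% | 0.6 | 0.69 | 51% |
| 30% / 40% | 0.8 | 0.59 | 84% |
| 30% / 40% | 0.6 | 0.57 | 87% |
| 20% / 50% | 0.8 | 0.56 | 89% |
| 20% / 50% | 0.6 | 0.52 | 96% |

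The planned chi-squared test carries no stated correction. Without one, power at 103 per arm is 84% with equal uptake and 73% for the 50/20, r = 0.8 case. The risk ratios do not depend on this choice.

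**The case against.** The strongest reply is that every link is conditional. The Background describes premedication in general, not practice at Chilaw, Anuradhapura or Peradeniya, and calls its efficacy controversial. Bias needs three things together: that these hospitals premedicate, that use differs by arm, and that the drugs work. The protocol shows none of them. If premedication is routine at a site, it may go to everyone who receives antivenom, and equal use creates no bias. The protocol also refers to a current protocol for antivenom reactions, which is not shown and might cover prophylaxis. All of this stands, and it limits the point to a risk.

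A reader might infer that the trial is biased towards no difference, because the Background says that "rapid infusions may cause complement mediated reactions" and a clinician who believes this would premedicate the fast arm more. That direction is plausible, but it is an inference about behaviour from a remark on mechanism. The reverse is possible and would inflate the effect, so no direction can be assigned.

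The double-blind label in the Research Plan does not answer the point. The same section says open label, the slip states the duration, and no masking is described.

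Nor can the matter be left to the statistical analysis plan, since a rule for drugs given at the bedside has to be in place before the data exist.

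**Conclusion.** The point holds as a low-severity gap in conduct. The protocol discloses the arm before antivenom starts and neither fixes nor records a co-intervention aimed at the primary outcome, so arm-dependent premedication is possible and would go unseen.

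Size and direction are unknown. With 50% vs 20% uptake and a premedication risk ratio of 0.8, a true ratio of 0.60 would be seen as 0.64 or 0.56, depending on which arm is premedicated more; power at 103 per arm would be 68% or 89% instead of 80%. A 10-point difference in uptake moves the ratio by at most about 0.03 for r between 0.6 and 0.8. There is no bias if uptake is equal or premedication is ineffective. These figures rest on assumed uptake and efficacy and on the protocol's 50% vs 30%.

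The stronger conclusion, that the comparison is biased or that the trial must forbid or standardise premedication, is not supported by the document.

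**What to change.** In the detailed description of the research method, beside the randomisation step, add: the decision whether to premedicate, and with which agents, is written on the trial form before the envelope is opened and is followed in either arm; what was actually given is recorded with its time and the reason for any departure; premedication is reported by arm.

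The cost is one entry on the form and a slight limit on clinician discretion after allocation. A ban or one mandated regimen is not needed. Either would be a debatable change in care at three hospitals, overriding the admitting consultant on a contested safety measure, whereas deciding before the envelope is opened removes the route to bias while leaving the choice with the clinician.

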**Objectives:**

General Objective

To determine, whether slowing the rate of antivenom infusion will reduce the frequency and severity of antivenom reactions in patients with snake envenoming.

**Research Plan:**

**Study centre**: Base Hospital Chilaw, Anuradhapura, Peradeniya for a period of 12 months. It is an original study, **A randomized, open label, controlled clinical trial.** A total 240 patients will be recruited in this study.

A randomized, double-blind, controlled clinical trial with two parallel groups:

- 10 vials of polyvalent antivenom administered in Normal saline (500ml) over 20 minutes*
- 10 vials of polyvalent antivenom administered in Normal saline (500ml) over 2 hours*

If the patient is administered more than 10 vials then this will be given at the same rate =10 vials over 20 minutes or 2 hours (Although the volume and dilution can be modified for convenience).For example 20 vials given over 40 minutes in 500 ml of Normal saline.

**ii. Detailed description of the research method.**

All patients bitten by a snake will be eligible for the study and will be approached at the time of admission, however they will not formally enter the interventional trial until the decision is made to administer antivenom. All eligible patients will have baseline clinical data collected, including clinical symptoms, signs and a 20 minute whole blood clotting test (20 WBCT). Baseline blood will be collected (see below). When a decision to administer antivenom is made, the patient will be randomized to one of the two parallel treatment arms. Patients in the first treatment group will receive 10 vials of antivenom in 500 ml of normal saline over 20 minutes [alternatively 20 vials of antivenom in 500 ml of normal saline over 40 minutes] Patients in the second treatment group will receive 10 vials of antivenom in 500 ml of normal saline over 2 hrs [alternatively 20 ampoules of antivenom in 500 ml over 4 hours.]

Randomisation will be done by computer in blocks of four (eg. AABB, ABAB etc.) using Microsoft Excel. The computer generated list will be used to randomize pieces of papers to sequentially ordered envelopes with the wording “20 minute infusion” or “2 hour infusion”

Patients will be closely observed for the four hour period following the commencement of administration of antivenom. The patient will be put on a cardiac monitor for this period if possible. For the first hour, HR, BP, RR, oxygen saturation and temperature will be measured every 5 minutes and then every hour for the remainder of the four hours. Patients will be observed for evidence of an allergic reaction using the Brown grading system,(10) including auscultation of the chest. Allergic reactions will be treated as per the current protocol of antivenom reactions with intravenous fluids and 0.5 mg of intramuscular adrenaline into the lateral thigh (or upper arm if not possible).

A 15 mL sample of blood will be taken using a sterile technique (syringe and needle) from each patient.

- 1. The 15mL sample will be divided between one serum (red top tube), one EDTA tube (purple top) and one plasma citrate (blue top) tube.
  2. The serum tube will be spun and the serum aliquoted into 3 portions and frozen.
  3. The citrate plasma tube will be immediately double spun and then aliquoted into two separate tubes and immediately frozen.
  4. The EDTA tube will be spun and aliquoted into two separate containers.

The specific identity of the snake will be determined by ELISA on blood samples and blood concentrations will be determined with the same method retrospectively.(11) Normal coagulation studies will be performed on samples for patients who developed coagulapthy. Creatine kinase will be measured in patients with Russell’s viper bite. Serial mast cell tryptase, complement and anaphylactic mediators will be measured in all patients who receive antivenom. Urine will be collected in patients with Russell’s viper bite. If the snake is brought to the hospital this will be photographed or formally identified and recorded. Blood films will be made where possible and stored for the study.

Throughout the trial, the patient will remain under the responsibility of the admitting consultant. Both study and host hospital clinicians will report to this individual.

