**Explain recruitment procedures:**

Team members will be on 24hrs a day in the study hospitals. They will be notified of any snake bite admissions by the doctor on duty in the OPD or by the medical wards so they can recruit the patients. Chilaw, Anuradhapura, Peradeniya hospitals manage about 500 snake bite patients annually and of these approximately 50% will receive antivenom. Past experience of poisoning trials in Sri Lanka suggest a high recruitment rate (>90% in a trial of anti-digoxin Fab RCT(9)); so we would conservatively estimate 80% patients would be recruited. This means that 200 patients will be recruited over a one year period.

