**Inclusion and exclusion criteria.**

Study will recruit all patients that have a history of snake bite and randomize all patients that then receive antivenom. The exclusion criteria will be

- Age < 14 years
- Pregnancy
- Previous administration of antivenom

All appropriate methods have been used to avoid bias:

1. Randomization method is independent of the investigators and dependent on a computer algorithm;
2. Treatment allocation cannot be predicted in advance
3. The primary and secondary outcomes are objective measures
4. All outcomes will be recorded prospectively by the study team and not by the treating doctors
5. Patient follow-up will be complete
6. Analysis will be by intention to treat.

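### The protocol calls the trial both open label and double-blind, and its single published block size of four does not support the claim that allocation cannot be predicted

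*Protocol*

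**What the plan says.** Protocol, Research Plan, gives two design labels: "A randomized, open label, controlled clinical trial" and, shortly after, "A randomized, double-blind, controlled clinical trial with two parallel groups". The arms listed beneath are "10 vials of polyvalent antivenom administered in Normal saline (500ml) over 20 minutes" and "10 vials of polyvalent antivenom administered in Normal saline (500ml) over 2 hours". No dummy infusion, screen or other masking is described.

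The section giving the detailed description of the research method states: "Randomisation will be done by computer in blocks of four (eg. AABB, ABAB etc.) using Microsoft Excel". The list is transferred to paper slips in sequentially ordered envelopes, and each slip names the infusion duration. No other block size is mentioned. The protocol does not say whether the three hospitals share one list or each have their own.

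The bias list under Inclusion and exclusion criteria gives this as a safeguard: "Treatment allocation cannot be predicted in advance". The same list says that the study team, not the treating doctors, records outcomes. Under Explain recruitment procedures, team members on site also do the recruiting.

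**The concern.** There are two linked faults.

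First, the trial cannot be both open label and double-blind. A bag that runs for 20 minutes and one that runs for 2 hours are distinguishable at the bedside, so a reader who relies on the second label credits the trial with a protection that it lacks.

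Second, permuted blocks conceal the next allocation only as long as earlier allocations or the block boundaries are hidden. Here the block size is printed in the protocol, the envelopes run in order, and the people who recruit can see which infusion earlier patients at their hospital received. The last place in a block, and sometimes the third, can then be worked out before the envelope is opened.

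Someone who knows the next arm could, deliberately or not, influence which patients are entered and when. That is selection before randomisation, and analysis by intention to treat does not repair it.

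**Working it through.** The protocol gives no figure for predictability, so there is none to reproduce. Its sample size calculation plays no part here.

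**Inputs**
- Two arms and blocks of four (Detailed description of the research method). The examples AABB and ABAB imply two of each arm per block.
- Planned total of 240 (Research Plan; How the sample size was determined).
- Three hospitals (Research Plan).
- Assumption for the upper figure: the observer knows the block size and has seen all earlier allocations in the block.

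**Allocations certain in advance**

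There are 4!/(2!·2!) = 6 equally likely blocks. An allocation is certain once one arm is used up in the block.

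| Position | Certain when | Blocks out of 6 | Probability |
| --- | --- | --- | --- |
| 1 | never | 0 | 0 |
| 2 | never | 0 | 0 |
| 3 | first two match | 2 | 1/3 |
| 4 | always | 6 | 1 |

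Share certain = (0 + 0 + 2 + 6)/24 = 8/24 = 1/3. For 240 patients, 240 × 1/3 = 80.

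**Correct guesses when always naming the arm that is behind**
- Position 1: 1/2.
- Position 2: 2/3 (two of the three remaining places belong to the other arm).
- Position 3: certain with probability 1/3, otherwise tied, so 1/3 + (2/3)(1/2) = 2/3.
- Position 4: 1.

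Mean = (1/2 + 2/3 + 2/3 + 1)/4 = 17/24 = 70.8%, against 50% under simple randomisation.

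**One list shared by the hospitals, staff seeing only their own patients**

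Assume that staff know the envelope numbers and that each patient comes from hospital s with probability p_s.
- Position 3 is certain if all three patients so far are from one hospital and the first two match: (1/3)·Σp_s³.
- Position 4 is certain if the two earlier patients of the used-up arm are from the same hospital as the fourth: Σp_s³.
- Share certain = [(1/3)Σp_s³ + Σp_s³]/4 = Σp_s³/3.

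| Recruitment split (assumed) | Σp_s³ | Share certain | Of 240 |
| --- | --- | --- | --- |
| equal thirds | 1/9 | 3.7% | about 9 |
| 60/20/20 | 0.232 | 7.7% | about 19 |
| 80/10/10 | 0.514 | 17.1% | about 41 |
| one list per hospital, or allocations shared across sites | 1 | 33.3% | 80 |

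A simulation of the equal split also gave 3.7%.

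**Other block schemes, all earlier allocations seen**

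| Scheme | Certain | Best guess correct |
| --- | --- | --- |
| fixed 4 | 33% | 71% |
| fixed 6 | 25% | 68% |
| fixed 8 | 20% | 67% |
| random mix of 4 and 6, boundaries unknown (simulated) | about 5% | not calculated |
| random mix of 4, 6 and 8, boundaries unknown (simulated) | about 2% | not calculated |

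Undisclosed mixing removes most of the certainty. The results for fixed 6 and 8 suggest that some advantage in guessing would remain.

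**The case against.** **The one-in-three figure is conditional.** It needs an observer who knows the block size and sees every earlier allocation in the block. A reader might infer that 80 patients' allocations will be known in advance. The documents do not support that, because they do not say how the list is divided among the hospitals. Under one shared list with equal recruitment and only own-site patients seen, the figure is about 4%. This objection stands, and the result has to be given as a range.

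**The route to bias is not shown in full.** A reader might infer that consent is sought after the decision to give antivenom, which would leave an opening at that moment. The text does not say so: patients are approached at admission and randomised once the decision is made. The protocol also intends to randomise everyone who receives antivenom, and it leaves patients under the admitting consultant. Nothing shows that whoever decides on antivenom also holds the envelopes. This stands as a limit: there is an opening for bias, and no bias is demonstrated or measured. The opening is not closed, however. The recruitment section itself expects about 80% of some 250 antivenom recipients (500 × 50%) to be recruited, which leaves about 50 not entered.

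**Dose.** A reader might add that foreknowledge could shift the dose. Because the arm is visible once allocated, dose could respond to it under any block size, so this is not a consequence of the blocks.

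**The blinding label may look like a slip of wording.** Open label appears in the same section, the bias list does not claim blinding, and no analysis depends on it. That limits the harm, but the two labels still contradict each other.

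**Conclusion.** Both parts hold in limited form. Double-blind is wrong for the design described. The assurance that allocation cannot be predicted is not supported by the method: even in the most favourable case worked above, about 4% of allocations can be certain in advance, and the share can reach one third (about 9 to 80 of 240).

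The upper figures of 33% and 71% rest on knowledge of the block size and sight of all earlier allocations in the block. The lower figure rests on an assumed shared list, equal recruitment and no exchange of allocations between sites. The protocol does not settle which applies.

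The documents do not show that selection bias will occur or how large it would be. The sample size is unaffected. The correction is worth making because it is cheap and removes most of the certain foreknowledge.

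**What to change.** 1. Delete double-blind under Research Plan and keep open label.
2. Replace the single block size with randomly varying sizes. Do not disclose them to recruiting staff, and remove them from the protocol text that those staff hold.
3. State whether there is one list or one per hospital. Separate lists alone would raise local predictability compared with a shared list, so they should be used only together with step 2.
4. Specify sealed, opaque, numbered envelopes, opened only after eligibility, consent and the decision to give antivenom have been recorded.
5. Reword the assurance in the bias list so that it claims no more than this procedure delivers.

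A hospital-stratified analysis is not part of this remedy, since it does nothing about predictable allocation.

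The cost is a new computer-generated list, new envelopes and a few lines of protocol text. The downside is a slightly larger possible imbalance between arms.
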